## Abstract

**Background:**

There is a dearth of empirical evidence on the effectiveness of pharmacological and non-pharmacological treatments for adolescents with posttraumatic stress disorder (PTSD) in developing countries. The primary aim of the study is to examine the effects of prolonged exposure therapy compared with supportive counseling for adolescents with PTSD delivered by nurses trained as counselors.

**Methods/design:**

A single-blind randomized clinical trial comprising 90 adolescents with PTSD using a permuted block design will be utilized. Nurses previously naïve to prolonged exposure and supportive counselling will be trained to provide these treatments at the adolescents’ high schools. Data collection will last from March 2014 to December 2017 and annually thereafter, dependent on the availability of funding.

Participants will receive seven to fourteen 60 min sessions of prolonged exposure treatment (*n* = 45) or supportive counselling (*n* = 45). All assessments will be conducted before treatment, at mid-treatment, immediately after treatment completion, at 3-, 6-, and 12-month follow-up, and annually thereafter. It is hypothesized that PE-A will be superior to SC in reducing PTSD symptoms at post-treatment as measured by the CPSS-I administered by an independent evaluator. It is further hypothesized that PE-A treatment gains will be maintained at 3-, 6- and 12-month follow-ups and annually thereafter.

**Discussion:**

While early indications are that PE-A is an effective treatment for PTSD in adolescents, this study will help determine the effectiveness of PE-A in a South African, community setting (school-based) when task-shifted to nurses, as compared to SC.

**Trial registration:**

Pan African Clinical Trials Registry: PACTR201511001345372, retrospectively registered 11 November 2015.

**Electronic supplementary material:**

The online version of this article (10.1186/s12888-018-1873-x) contains supplementary material, which is available to authorized users.

## Background

Experiences that may be perceived as traumatic, such as experiencing or witnessing either physical abuse, sexual assault, or other forms of violence, are common occurrences among children and adolescents around the world. In school samples in the United States, the prevalence rates of exposure to potentially traumatic events is reportedly between 40 and 70% [1, 2] and in a national study of 2000 children aged 10–16, 24% endorsed being victims of physical assault, sexual assault, or kidnapping [3].

In South Africa, a study conducted in a rural setting found that 67% of children had directly or vicariously experienced a traumatic event [4]. Another, conducted on 10–16-year-old children in a low-income area in Cape Town, found that 95% had witnessed violent events and 56% had experienced violence themselves [5].

In addition to prevalence studies of exposure to traumatic experiences, the literature suggests that adolescents are at an increased risk of developing PTSD with the diagnosis peaking in late adolescence [6].

Two studies conducted in Cape Town, South Africa showed that between 20 and 25% of adolescents met criteria or sub-threshold criteria for PTSD [7, 8] with the most likely pathogenic events identified as sexual assault, physical assault by a family member, and serious accidents. In another South African study of children and adolescents (mean age of 14.3 years) exposed to at least one lifetime potentially traumatic experience, sexual abuse was reported in 53% of participants (42.6% females, 10.6% males), with 64% of violations committed by perpetrators who were known to them [9].

PTSD is often characterized by comorbidity. With the most common co-occurring psychiatric disorder depression [10–13]. The prevalence of depression among adolescents diagnosed with PTSD is reported to be as high as 41% [1, 9]. This is much higher than the rate of depression (8%) amongst their peers [1]. Other common co-occurring diagnoses are separation anxiety disorder, social anxiety disorder, specific phobias, panic disorder, generalized anxiety disorder, and substance abuse disorders [1, 14]. Adolescents who have been assaulted sexually or physically may experience relationship difficulties with peers and caregivers, weaker school performance and behavioral issues [13]. Additionally, those with PTSD may display anger, aggression, self-destructive behaviors, and sexually inappropriate or high-risk behaviors [14], can feel isolated, stigmatized, often struggle with low self-esteem and experience difficulty trusting others [14].

Given the prevalence of PTSD in South Africa and its chronic and debilitating effects in children and adolescents if left untreated, it is a disorder that warrants attention [15, 16]. PTSD can lead to long-term personal suffering that reaches beyond adolescence into adulthood. It can also have serious public health, social and economic implications. In low- and middle-income countries (LMIC’s) there are challenges to both access to and availability of treatment, in particular psychological treatment [8, 17–21] for disorders such as PTSD. This dearth, among other factors, may be attributed to the lack of available skilled treatment providers and concerns among skilled professionals regarding the generalizability of treatments typically developed in higher income, ‘western’ cultural academic settings [19].

Studies have suggested the feasibility of task-shifting the delivery of treatment to community settings and utilizing the services of appropriately trained and supervised non-specialized primary care health workers (NSHWs) [19]. Identifying effective psychological treatments that can be delivered by NSHWs is one of the leading research priorities in the global mental health arena [22]. To demonstrate their portability, evidenced-based trials demonstrating the effectiveness of the task-shifted treatment in LMICs must precede their implementation [20]. The current study aims to provide evidence that both Prolonged Exposure for Adolescents (PE-A) and Supportive Counseling (SC) can be task-shifted to nurses within a community setting for adolescents (i.e., schools).

## Rationale/motivation & originality

Studies conducted to date indicate that trauma-focused cognitive-behavioral therapy (CBT) is an effective treatment for the aftermath of trauma in younger children with sexual abuse trauma [23–29], and other types of trauma [30–32]. Some of these studies were not randomized control trials (RCTs) and most only included younger adolescent participants. It is, therefore, prudent to test the efficacy of trauma-focused CBT in an RCT with adolescents spanning a wider age range (and including older adolescents).

Prolonged Exposure (PE) therapy is a trauma-focused, exposure-based treatment initially developed for adults with PTSD following exposure to diverse types of trauma. There is good empirical support for this therapy, including many RCTs [33]. Due to the relative ease of training, PE has been widely disseminated around the world and following a relatively brief training, non-specialists have been taught to successfully provide PE [34, 35]. PE for adults has been shown to be effective within a community setting [35] and meets the requirements for dissemination. Prolonged Exposure therapy for Adolescents (PE-A), which was based on the adult protocol, also appears to meet these requirements as has been demonstrated in community settings in the USA [36] and in Israel [37]. The comparator treatment, SC, is a non-trauma focused treatment that is widely used in crisis centers and community settings to treat sexually abused children and other traumas [26].

A pilot and feasibility study on psychological treatment of PTSD within a community setting (schools in Cape Town, South Africa) utilizing the services of NSHWs (previously treatment-naive nurses), [38] provided early indications that task-shifting of PE-A and SC for PTSD can be successful.

To our knowledge, there are no other published RCTs for the treatment of PTSD in any population or age group in South Africa. A literature review of all CBT research conducted in South Africa to date, identified 15 studies, with most comprising of a single case design [39].

The proposed research aims to examine the effectiveness of a psychotherapeutic intervention, administered by NSHW’s, to treat the symptoms of PTSD in adolescents exposed to trauma. The study aims are to compare the efficacy of two active treatments, PE-A and SC, in reducing PTSD and other psychopathology symptoms (e.g., depression, anger, other anxiety disorder symptoms, general psychopathology, and global dysfunction), and to examine the relationship between change in PTSD symptoms and change in distress-related cognitions and emotions (e.g., affect regulation, trauma-related cognitions, self-attributions). We also aim to explore whether moderators (e.g., pre-treatment psychopathology, education, parental distress, resilience, self-esteem, perceived social support) and mediators (e.g., treatment satisfaction) are associated with treatment outcome. A further aim of the study is to explore the ability of newly trained counselors (previously treatment naïve), to adequately provide the treatments by adhering to the PE-A and SC treatment manuals. In keeping with international trends to undertake RCTs in naturalistic settings rather than within specialist academic institutions, the present RCT will take place within a community setting, namely, at local schools.

A sub-sample of participants, counselors and teachers who will be involved in the first year of treatment will be contacted during the second year to participate in the qualitative assessment of their subjective experiences by using a nested qualitative component. Triangulation will be employed as it has previously been used to evaluate school mental health program efficacy [40–42] by including semi-structured interviews and focus groups looking at feasibility (barriers/facilitators), acceptability (like/dislike), and impact (pros/cons) as experienced by stakeholders. Although there is literature about the process of seeking mental health treatment as a minor [43] and a quantitative measure to evaluate a youth’s experience with mental health services exists, this will be the first study describing the subjective experiences of adolescents accessing treatment for PTSD.

The study is unique in that it will be the first RCT of CBT in an adolescent population to be conducted within the South African context and that involves task-shifting by identifying counsellors, training and supervising them in a treatment protocol that was originally intended for use and administration by qualified specialized psychologists. It will utilize independent evaluators for the treatment outcome assessments and will examine treatment protocol adherence with independent fidelity ratings.

## Objectives

### Research hypothesis

PE-A will be superior to SC as administered by counsellors in reducing PTSD symptoms at post-treatment as measured by the Child PTSD Symptom Scale – Interview (CPSS-I).PE-A treatment gains will be maintained at 3-, 6-, and 12-month follow-up and annually thereafter as measured by the CPSS-I

### Secondary hypothesis

At post treatment PE-A will be superior to SC in reducing depression, anger, anxiety, general psychopathology, and global functioning.PE-A treatment gains will be maintained at 3-, 6-, and 12-month follow-up and annually thereafter on measures of depression, anger, anxiety, general psychopathology and global functioning.irrespective of treatment assignment (PE-A or SC), reduction in PTSD symptoms at post-treatment will be significantly and positively correlated with reduction in distress-related cognitions and emotions

### Primary objectives

To compare the effectiveness of two treatments administered by counsellors, PE-A and SC, in reducing PTSD symptom severity over 7–14 sessions of treatment.to assess maintenance of PE-A treatment gains on PTSD symptom severity by conducting follow-up assessments at 3-, 6- and 12-month follow-up, and annually thereafter

### Secondary objectives

To compare the effectiveness of two active treatments, PE-A and SC, in reducing other psychopathology symptoms (e.g. depression, anger, general psychopathology and global functioning).To assess the maintenance of PE-A treatment gains on secondary outcomes by conducting follow-up assessment at 3-, 6-, 12-month follow-ups and annually thereafter.To examine the relationship between change in PTSD symptoms and change in distress related cognitions and emotions (affect regulation, trauma-related cognitions, and self-attributions).To assess counsellors’ adherence to the PE-A and SC treatment manuals.To evaluate the impact of moderators (e.g. pre-treatment psychopathology, education, resilience, severity of trauma, trauma-related distress, parental distress, social support, self-esteem) and mediators (e.g. treatment satisfaction, compliance, expectation) on outcome.to describe stakeholders (nurses, teachers, adolescents) and their experiences (training, implementation of treatment, access to treatment, barriers, and facilitators to successful implementation) to inform project scalability

## Method

### Design

The study design is reported in line with the SPIRIT 2013 Statement (Explanation and elaboration: Guidance for protocols of clinical trials) [44].

Figure 1 provides an overview of the study design.

**Fig. 1 Fig1:**
[figure not shown]
Study Consort Diagram, Consort diagram

A single-blind permuted block randomized control design will be used. The proposed research aims to examine the effectiveness of a psychotherapeutic intervention administered by counsellors to treat the symptoms of PTSD in adolescents exposed to trauma. The aim is to conduct a randomized controlled trial (RCT) to compare PE-A to SC to determine the comparative effectiveness in reducing PTSD and associated symptoms in adolescents.

The study will compare the efficacy of PE-A to SC. Participation will be voluntary. All participants, who meet full PTSD or sub-threshold PTSD criteria, will be scheduled for a pre-treatment assessment with Independent Evaluators (IE). The one IE will be an experienced diagnostician and clinical psychologist and the other an experienced psychiatric nurse. Adolescents will be randomly assigned on a 1:1 ratio to receive either PE-A or SC.

Treatment will consist of 7–14 sessions of either PE or SC. The number of sessions each participant receives will be based on the weekly self-report measure of PTSD symptoms (Child PTSD Symptom Scale – Self Report; CPSS-SR); however, this will range between a minimum of 7 sessions to a maximum of 14 sessions. A 70% symptom reduction is chosen as sufficient for treatment termination.

After session five, all participants will receive a mid-treatment evaluation by the IE. The IE will again assess the participants upon termination of treatment. Participants will then enter the non-treatment follow-up phase. Participants who prematurely terminate therapy (before 70% symptom reduction or 7 sessions) will undergo a post-last session assessment with the IE and will then enter the follow-up phase. Follow-up assessments will be conducted at 3-, 6-, and 12 months post-treatment and annually thereafter. The IE assessments will comprise both structured clinical interviews and self-report measures. The assessments will cover PTSD severity, related psychopathology, general psychopathology, and PTSD-related cognitions. At the 12-month follow-up, participants who receive SC and are deemed to still have clinically significant PTSD symptoms (as determined by the IE at 12-month follow-up assessment), will be offered PE-A. To add to the rigor of the study and demonstrate the long-term efficacy of the intervention, there will be annual posttreatment follow ups, dependent on the availability of funds for this purpose.

A cross-sectional qualitative evaluation will take place during the follow up assessments of the adolescents who have completed their treatment. Adolescents who participated in the study in the preceding year (regardless of completion or outcome) will be invited to participate in semi-structured interviews with an independent psychologist. Similarly, there will also be separate focus groups for the nurse counsellors and the contact persons at the schools who had been part of the study during the preceding year.

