#### General considerations for data analysis

Descriptive statistics will be gathered in order to determine if variables have a normal distribution and variables that violate assumptions of normality will be transformed. If this does not improve the normality of distribution, distribution free statistics will be used.

The study has pre-, mid-, post-treatment, three follow-up assessments and annual follow-up thereafter. This creates clustered data due to repeated measures. To examine treatment difference, generalized estimating equations (GEE) and a linear mixed-effects model approach (LMM) will be employed. Both approaches accommodate missing data. LMM will be the main analytical tool, particularly for estimating between-participant variability; GEE will be used to assess the robustness of the population parameters, such as treatment effects.

Analyses correlating the change in PTSD symptoms with each of the distress-related cognition and emotion variables at post-treatment will be performed, by pooling data across treatment conditions. Product-moment and Spearman’s rho correlation coefficients will be used.

Correlation analyses correlating the change in PTSD symptoms with each of the distress- related cognition and emotion variables at post-treatment, by pooling data across treatment conditions, will be performed. Product-moment and Spearman’s rho correlation coefficients will be used.

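### The primary maintenance hypothesis has no last visit and runs into funding-dependent annual visits after PE-A has been offered to symptomatic SC participants, so those visits cannot support a claim of long-term efficacy relative to SC alone

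*Protocol article*

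**What the plan says.** All references are to the protocol article.

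- **Research hypothesis.** The between-arm claim is tied to one time point: "PE-A will be superior to SC as administered by counsellors in reducing PTSD symptoms at post-treatment". The maintenance claim beside it has no last visit: "PE-A treatment gains will be maintained at 3-, 6-, and 12-month follow-up and annually thereafter as measured by the CPSS-I".
- **Primary objectives.** The follow-up objective has the same open end: "to assess maintenance of PE-A treatment gains on PTSD symptom severity by conducting follow-up assessments at 3-, 6- and 12-month follow-up, and annually thereafter". The secondary hypotheses and objectives repeat the pattern for the other outcomes.
- **Funding.** The Abstract describes collection up to December 2017 and then "annually thereafter, dependent on the availability of funding". The Design section makes the annual visits "dependent on the availability of funds for this purpose", and the note under Table 3 in Measures says the same.
- **Offer of PE-A.** In the Design section, "participants who receive SC and are deemed to still have clinically significant PTSD symptoms" at the 12-month follow-up, as judged by the independent evaluator, will be offered PE-A. The next sentence gives the purpose of the later visits: "To add to the rigor of the study and demonstrate the long-term efficacy of the intervention, there will be annual posttreatment follow ups".
- **General considerations for data analysis.** The assessments are listed as pre-, mid- and post-treatment, "three follow-up assessments and annual follow-up thereafter". The linear mixed model (LMM) and generalised estimating equations (GEE) are then named as the means of comparing the treatments.
- **Protection against risks.** Here the offer of PE-A to SC participants with persisting PTSD or symptoms is placed when treatment ends, not at 12 months.

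**The concern.** Three features combine badly. The primary maintenance hypothesis includes visits that may never take place and has no final visit. Those visits come after an offer made to one arm only and triggered by poor outcome. They are nevertheless said to demonstrate efficacy, and they are listed with the data used to compare the arms.

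From the first annual visit after month 12, the SC arm would be a mixture of participants who did well on SC and participants who did badly and may since have had PE-A. A lasting PE-A advantage could then seem to fade only because SC participants received PE-A. Conversely, if PE-A scores stayed low, there would be no intact SC group to show whether untreated recovery would have produced the same result. At stake is how any statement about results beyond 12 months may be read.

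**Working it through.** The protocol gives no figure for this point. The check compares passages first; two hypothetical calculations then show how the size depends on uptake.

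**1. Order of events, on the Design section's timing.** Post-treatment, then 3, 6 and 12 months, then the offer to symptomatic SC participants, then the annual visits. No annual visit precedes the offer.

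**2. What runs on past 12 months.** Superiority over SC is placed at post-treatment. What continues is maintenance in the PE-A arm. The offer does not change what PE-A participants receive, so their scores can still be described. It does remove the unswitched comparator.

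**3. What the models take in.** The analysis section does not limit the LMM and GEE comparison to visits through month 12. As written, post-offer data belong to the repeated measures.

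**4. Timing conflict.** Design places the offer at 12 months; Protection against risks places it at the end of treatment. If an offer can come before month 12, the 3-, 6- and 12-month contrasts are exposed too.

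**5. Hypothetical A: power.** Inputs from the Sample size section: 64 completers, 80% power, two-tailed alpha 0.1, 30% dropout, 90 entrants. Check: 90 × 0.70 = 63, and 64 / 0.70 = 91.4, so 92; both are within two of the stated figures. No effect size is given. Treating the 64 as 32 per arm in a comparison of two means (an assumption):

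d = (1.645 + 0.842) × √(2/32) = 0.62

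Let a share c of the SC arm take PE-A and gain its full effect, with all 64 still observed. Then d after = 0.622 × (1 − c), and power = Φ(d after / 0.25 − 1.645).

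| c | d after | power |
|---|---|---|
| 0 | 0.62 | 80% |
| 0.1 | 0.56 | 72% |
| 0.3 | 0.44 | 54% |
| 0.5 | 0.31 | 34% |
| 0.7 | 0.19 | 18% |

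**6. Hypothetical B: CPSS-I points.** All inputs are assumed: PE-A mean 9, SC mean μ = 13 or 15, SD 8, scores floored at 0, PE-A offered at a score of 11 or more, uptake u of 50% or 75%, further fall f of 30% or 50% in those who switch. The value 11 is the scale's diagnostic cut-off in Measures; the protocol does not make it the trigger for the offer.

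- Floored mean = μΦ(μ/8) + 8φ(μ/8), giving 9.52 for PE-A and 13.18 or 15.09 for SC. Difference before the offer: 3.7 or 5.6.
- Share eligible p = Φ((μ − 11)/8) = 0.60 or 0.69.
- Mean score of those eligible m = μ + 8φ((11 − μ)/8)/p = 18.2 or 19.1.
- Difference after = difference before − p × u × f × m.

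| u | f | from 3.7 | from 5.6 |
|---|---|---|---|
| 50% | 30% | 2.0 | 3.6 |
| 50% | 50% | 0.9 | 2.3 |
| 75% | 30% | 1.2 | 2.6 |
| 75% | 50% | −0.4 | 0.6 |

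The loss runs from about 35% to just over 100%. The one sign change needs the most extreme combination, in which switchers fall by 0.5 × 18.2 = 9.1 points, about 2.5 times the assumed arm difference.

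**The case against.** The strongest reply is that the protocol never hypothesises superiority over SC at the annual visits. What it carries forward is maintenance within PE-A, which an offer to the other arm leaves untouched. That stands. A reader might infer that long-term efficacy cannot be shown at all at these visits. The document does not support that: PE-A scores can be described, and an as-randomised contrast remains valid for PE-A versus SC followed by optional PE-A. What is lost is efficacy relative to SC alone.

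A reader might also infer that the primary hypothesis as a whole has no point of decision. That goes too far. The superiority part is decided at post-treatment, the maintenance part names 3, 6 and 12 months, and the main collection period is dated. Only the annual extension is open, and its funding condition is stated openly.

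A third inference would be that annual data will distort the estimated trend through month 12. That depends on how time is coded, which the article does not say and which an analysis plan commonly settles. Handling of data after a switch may be settled there too.

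The reply does not dispose of the point. The protocol describes its efficacy question as a comparison of PE-A with SC, so the stated purpose of the annual visits reads as comparative. The analysis section places those visits with the data for the arm comparison. The open-ended hypothesis is in the protocol's own text and is not a detail left to another document.

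**Conclusion.** The point holds as one of wording and analysis scope. The maintenance hypothesis and objective have no last visit, they include visits that depend on funding, and on the Design section's timing all those visits follow selective access to PE-A in the SC arm. The claim to demonstrate long-term efficacy is therefore too strong as a comparative statement: the contrast after the offer answers a different question, and PE-A scores alone do not separate treatment effect from natural course.

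The size cannot be fixed from the document, because uptake of the offer and its effect in those who accept are not given. Both calculations are hypothetical. They show dilution that grows with uptake; with switchers gaining exactly the PE-A effect, the difference vanishes only as uptake across the SC arm nears 100%.

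The post-treatment superiority test is not affected. The 3-, 6- and 12-month contrasts are unaffected only if no offer is made before the 12-month assessment, and the two passages on timing leave that open. The point should be corrected, but it does not threaten the main between-arm comparison.

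**What to change.** 1. Name 12 months as the last confirmatory visit for the maintenance hypotheses and for the randomised LMM and GEE contrast. Remove the annual extension from the primary and secondary hypotheses and objectives.
2. Replace the stated purpose of the annual visits with a descriptive aim.
3. Analyse annual visits separately as exploratory, by original arm. Record the start date of any PE-A in SC participants and show those participants as an identified group. State that the as-randomised contrast at these visits estimates PE-A versus SC followed by optional PE-A.
4. Reconcile the Design section and Protection against risks on when PE-A is offered. If the offer can come before month 12, the last confirmatory between-arm time point must be one that precedes it.

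The cost is wording, a narrower scope for the main model and one recorded date. No visit is dropped. The downside is that the confirmatory claim stops at the named visit.
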